### Sample size

We based our sample size calculation on a non-inferiority design. The Olerud-Molander score (OMAS) will serve as primary outcome measure. We have used the results from an earlier study on this subject for our sample size calculation [27]. For the sample size calculation we hypothesized an equal OMAS between the two groups. Using a one-sided significance level (α) of 0.025 and a power (ß) of 90% with a standard deviation (SD) of 19 points (derived from the study mentioned before) and setting our non-inferiority limit at 10 a total of 76 patients are needed in each study arm. Taking a 10% loss to follow-up into account, a total number of 167 subjects will be needed to demonstrate non-inferiority between the two treatment strategies. Furthermore we performed a sample size calculation for a subgroup analysis based on age. We hypothesize that the SD will be lower in these subgroups due to increased homogeneity, therefore we have used an SD of 16 for the sample size calculation of the subgroups. Using a significance level (α) of 0.05 and a power (ß) of 90% 88 patients are needed in each subgroup to prove non-inferiority. Taking 10% loss to follow-up into account a total of 193 patients need to be randomized.

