### Statistical analysis

The primary endpoint will be analysed according to the intention-to-treat and the per-protocol principle, non-inferiority will only be declared if both types of analysis prove non-inferiority. The primary endpoint will be analysed using a one sided test for non-inferiority with an alpha of 0.025. Descriptive methods will be used to assess quality of data, homogeneity of treatment groups and endpoints. Normality of the data will be analysed by visually inspecting the histograms. Secondary outcomes will be analysed using either a t-test or Mann-Whitney U test for continuous data according to the distributing of the data and a Chi Square test for categorical data. Missing data will be handled through multiple imputation with predictive mean matching. All analyses will be performed using the standard statistical software. Separate analyses will be performed on subgroups based on age. A multivariable analysis will be performed to identify predictors of worse functional outcome.

The CEA and CUA will be performed on the intention to treat data, with a time horizon of 12 months and from a societal perspective. The primary economic outcomes are the costs per quality adjusted life year (QALY) and the costs per point functional recovery improvement. Moreover a budget impact analysis (BIA) will be performed with a time horizon of 4 years. The questionnaires estimating the secondary outcome measures ‘resources utilization’ and ‘costs’ will only be used in patients included in the Netherlands due to practical feasibility and to ensure a valid outcome.

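### Each age subgroup is sized to prove non-inferiority at its own full one-sided 0.05, so the three tests together carry about a 10% chance of a false claim at the margin, although the primary test keeps its 2.5%

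*Protocol article*

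**What the plan says.** The Primary Outcome section names one primary outcome, the OMAS at 12 months. In the Sample size section the overall comparison is planned at: "Using a one-sided significance level (α) of 0.025". With an SD of 19, 90% power and no true difference, the text continues: "setting our non-inferiority limit at 10 a total of 76 patients are needed in each study arm". Adding 10% for loss to follow-up gives 167.

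The same section then adds a calculation for subgroups by age, with SD 16, alpha 0.05 (sidedness not stated) and 90% power. Its result is that "88 patients are needed in each subgroup to prove non-inferiority", and with 10% loss this raises the total to 193.

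The Statistical analysis section says: "The primary endpoint will be analysed using a one sided test for non-inferiority with an alpha of 0.025". For the primary endpoint it allows a declaration of non-inferiority only if the intention-to-treat (ITT) and per-protocol (PP) analyses both succeed. On age it says: "Separate analyses will be performed on subgroups based on age".

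**The concern.** Subgroups that are powered at 90%, described as able to prove non-inferiority, and allowed to set the size of the trial read as confirmatory. Each has its own alpha, and that alpha is more lenient than the one for the primary test. Followed as printed, the text permits a non-inferiority statement for one age group at a weaker standard of evidence than the trial's main conclusion requires, including when the overall comparison has failed.

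The Discussion intends the result to support a change in standard practice. A statement that on-demand removal is non-inferior in one age group could be used in the same way.

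**Working it through.** **Inputs.** From Sample size: margin 10, true difference 0, power 90%, SD 19 overall and 16 in subgroups, alpha 0.025 one-sided overall and 0.05 for subgroups. From Interventions: 1:1 allocation. Assumed: the margin of 10 also applies to the subgroups (no other is given), and there are two subgroups, matching the age strata under Randomisation (60 and over, under 60). The Abstract's 194 (80% power, 15% loss) rests on different inputs and is not used here.

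**Step 1: the plan's own figures.** Per arm, n = 2 × SD² × (z for 1 − alpha + z for power)² / margin².

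- Overall, one-sided 0.025: 2 × 361 × (1.960 + 1.282)² / 100 = 75.9, so 76 per arm and 152 in total; 152 × 1.1 = 167.2. The plan states 76 and 167.
- Subgroup, one-sided 0.05: 2 × 256 × (1.645 + 1.282)² / 100 = 43.9, so 44 per arm and 88 per subgroup. Two subgroups make 176; 176 × 1.1 = 193.6. The plan states 88 and 193.
- Subgroup, one-sided 0.025: 2 × 256 × (1.960 + 1.282)² / 100 = 53.8, so 54 per arm and 108 per subgroup. This is not the plan's figure.

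The printed 0.05 is therefore one-sided, twice the primary test's level, and is spent in full in each subgroup.

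**Step 2: chance of at least one false claim.** Suppose on-demand removal is truly worse by exactly 10 points in both age groups. The two subgroup statistics Z1 and Z2 are independent, and the overall statistic is √f × Z1 + √(1 − f) × Z2, where f is the share of patients in one age group. Then

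P(any claim) = P(any subgroup claim) + P(overall claim) − P(both).

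P(both) comes from simulation (4 million draws). For an even split:

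| Subgroup alpha, one-sided | Any subgroup claim | Overall claim | Both | Any of the three |
|---|---|---|---|---|
| 0.05 | 1 − 0.95² = 0.0975 | 0.0250 | 0.0225 | 0.100 |
| 0.025 | 1 − 0.975² = 0.0494 | 0.0250 | 0.0162 | 0.058 |

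A subgroup claim after a failed overall test has probability 0.0975 − 0.0225 = 0.075 at alpha 0.05, and 0.0494 − 0.0162 = 0.033 at 0.025. For age splits from 50:50 to 90:10, the last column ranges over 9.8-10.0% and 5.5-5.8%.

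**Step 3: effect of requiring both ITT and PP.** The documents give no correlation between the two analyses; 0.8 to 0.95 is assumed.

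| Rule applies to | Subgroup alpha 0.05 | Subgroup alpha 0.025 |
|---|---|---|
| Overall and subgroups | 5.1-7.6% | 2.7-4.2% |
| Overall test only | 9.8-9.9% | 5.3-5.5% |

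**Step 4: power if the subgroups were tested by Holm at a total one-sided 0.025.** The first step uses 0.0125. With 44 per arm and SD 16, the standard error is 16 × √(2/44) = 3.41. Power is Φ(10/3.41 − 2.241) = Φ(0.69), about 75%.

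**The case against.** The strongest reply is that the trial has one primary outcome and one declaration rule, that the age work is called a subgroup analysis, and that the Abstract and Discussion rest their conclusion on the overall comparison without mentioning age. Testing order and subgroup status are also commonly left to a statistical analysis plan, which is not shown.

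Much of this stands, and it rules out three stronger readings.

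- A reader might infer that the stated 2.5% is really 10%. It is not. The 0.025 is stated for the primary test only, later subgroup tests do not inflate it, and the article openly prints a different level for the subgroups.
- A reader might infer that the plan treats the three tests as equal routes to success. Nothing says that a subgroup result can carry the trial after an overall failure; the text only leaves that possible.
- A reader might count trials that fail overall yet succeed in one subgroup when the true difference is 0 in that age group and 10 points worse in the other. Nearly all such subgroup claims would be true, so that frequency is not an error rate.

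The reply does not remove the point, which does not depend on a missing testing policy. The printed text fixes the subgroup alpha at 0.05, gives proof of non-inferiority as the aim, and lets that calculation set the trial size. An analysis plan that called the subgroups supportive would have to contradict this text.

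**Conclusion.** The point holds as a problem with the status and error level of the age-subgroup claims. It is not a defect of the primary test. At the printed subgroup alpha, the chance of at least one false non-inferiority claim over the three tests is about 10%, of which about 7.5 percentage points are subgroup claims after a failed overall test. It falls to about 5-8% if the ITT-and-PP rule also governs the subgroups, and is about 6% at subgroup alpha 0.025 without that rule.

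These figures assume a true difference at the margin in both age groups, independent subgroups, a common margin of 10 and, for the 5-8%, an ITT/PP correlation of 0.8-0.95. They also assume that each test may be claimed on its own, which the text neither states nor excludes.

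**What to change.** In Statistical analysis, state that the overall 12-month OMAS comparison (ITT and PP, one-sided 0.025) alone decides non-inferiority, and that the age-subgroup results are supportive estimates with confidence intervals.

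In Sample size, remove the claim that the subgroups are sized for proof, and justify 193 as added precision for the subgroup estimates beyond the 167 needed for the primary test. On an even age split with SD 16, the 95% interval half-width per subgroup is 1.96 × 16 × √(2/44) = 6.7 points with 44 per arm (176 evaluable), against 1.96 × 16 × √(2/38) = 7.2 points with 38 per arm (152 evaluable).

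This takes a few sentences and no extra patients or data. The cost is that no stand-alone subgroup claim of non-inferiority can be made.

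If confirmatory subgroup claims are wanted, test them only after overall success in both ITT and PP, with Holm across the two at a total one-sided 0.025. Restate subgroup power as about 75% at the first step instead of 90%. The gate alone is not enough: with 0.05 kept per subgroup, if the overall result is truly non-inferior and one subgroup is at the margin, a false claim in that subgroup can still reach 5%.

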**Design:**

This is a pragmatic international multicentre randomised controlled trial in patients with an acute syndesmotic injury for which a metallic syndesmotic screw was placed. Patients will be randomised to either routine removal of the syndesmotic screw or removal on demand. Primary outcome is functional recovery at 12 months measured with the Olerud-Molander Score. Secondary outcomes are quality of life, pain and costs. In total 194 patients will be needed to demonstrate non-inferiority between the two interventions at 80% power and a significance level of 0.025 including 15% loss to follow-up.

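### The age-subgroup sample size uses twice the main calculation's one-sided alpha without a reason; at 0.025 its stated 90% power is about 83% (SD 16) or 69% (SD 19)

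*Protocol article*

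**What the plan says.** The Sample size section makes two calculations in one paragraph.

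- **Main comparison.** One-sided alpha 0.025, 90% power, SD 19 from an earlier study, and no true difference ("For the sample size calculation we hypothesized an equal OMAS between the two groups"). The margin and result follow: "setting our non-inferiority limit at 10 a total of 76 patients are needed in each study arm". With 10% loss the total is 167.
- **Age subgroups.** The SD is expected to be lower because patients within an age group are more alike: "therefore we have used an SD of 16 for the sample size calculation of the subgroups". With alpha 0.05 (sidedness not given) and 90% power, "88 patients are needed in each subgroup to prove non-inferiority". With 10% loss the total becomes 193.

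The Statistical analysis section says "The primary endpoint will be analysed using a one sided test for non-inferiority with an alpha of 0.025". It then announces separate analyses by age and names no alpha for them.

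The abstract (Design) gives a total of 194 at 80% power, "a significance level of 0.025" and 15% loss to follow-up.

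The Randomisation section stratifies by age, with a cut at 60 years, but sets no quota per age group.

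**The concern.** Two inputs change between the main and the subgroup calculation: alpha goes from 0.025 to 0.05 and the SD from 19 to 16. Both changes lower the required number. The first is not explained and the second rests on a hypothesis without data. The endpoint is the same, and no other margin is given for the subgroups.

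The paragraph therefore promises proof of non-inferiority in each age group on weaker evidence than the main claim requires. Someone who reads the subgroup results against a two-sided 95% confidence interval, as the primary test implies, would overestimate the chance of success. It matters more than a side remark would because the subgroup calculation raises the total from 167 to 193. The abstract then justifies almost the same total with a different alpha, power and loss.

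**Working it through.** **Inputs.** Margin 10, true difference 0, SD 19 (main) and 16 (subgroup), 90% power, alpha 0.025 (main) and 0.05 (subgroup), all from Sample size. Allocation 1:1, from Interventions.

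**Formula.** n per arm = 2 × SD² × (z for 1−alpha + z for power)² / margin², rounded up.

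**Reproducing the plan's figures**

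- Main, one-sided 0.025: 2 × 361 × (1.9600 + 1.2816)² / 100 = 75.9, so 76 per arm. This matches.
- Subgroup, 0.05 taken as one-sided: 2 × 256 × (1.6449 + 1.2816)² / 100 = 43.85, so 44 per arm and 88 per subgroup. This matches.
- Subgroup, 0.05 taken as two-sided (one-sided 0.025): 2 × 256 × (1.9600 + 1.2816)² / 100 = 53.8, so 54 per arm and 108 per subgroup. This does not match.
- Total: 2 × 88 = 176, and 176 × 1.1 = 193.6, against the stated 193.

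The subgroup 0.05 was therefore used one-sided.

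**Power with 44 per arm.** Power = Φ(margin / (SD × √(2/44)) − z for 1−alpha). The first term is 10 / (16 × 0.2132) = 2.93 at SD 16 and 10 / (19 × 0.2132) = 2.47 at SD 19.

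| SD | One-sided alpha | Power with 88 per subgroup | Per subgroup for 90% |
|---|---|---|---|
| 16 | 0.05 | 90.1% | 88 |
| 16 | 0.025 | 83.4% | 108 |
| 19 | 0.05 | 79.5% | 124 |
| 19 | 0.025 | 69.5% | 152 |

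The noncentral t gives slightly lower values at 0.025: 82.6% (SD 16) and 68.5% (SD 19). At one-sided 0.025, 88 patients reach 90% only if the SD is about 14.5 or lower.

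**What an SD of 16 implies.** Suppose 19 is the total SD in this population and age grouping alone brings it to 16. The variance between age groups is then 361 − 256 = 105, and 105/361 = 29% of the total. With a share p in one group, the difference in means is √(105 / (p(1−p))): 20.5 points at an assumed 50/50 split and 25.6 at an assumed 20/80 split.

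**The abstract's total**

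- Main inputs at 80% power and one-sided 0.025: 57 per arm; 114/0.85 = 134.1, so 135. This is not 194.
- Subgroup inputs (SD 16) at 80% power and one-sided 0.025: 2 × 256 × (1.9600 + 0.8416)² / 100 = 40.2, so 41 per arm and 82 per subgroup; 82/0.85 = 96.5, so 97; 2 × 97 = 194.

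The match is exact, but that the abstract's figure arose this way is an inference.

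**Unequal age groups.** All the powers above assume 88 evaluable patients in each stratum. If 30% of the 176 (about 53) fell in one stratum (an assumed share), power there at SD 16 would be 73% at 0.05 and 62% at 0.025.

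**The case against.** The strongest reply is that nothing is miscalculated. Alpha 0.05 and SD 16 are printed beside the result, and with the margin of 10 they give 88. The Statistical analysis section ties 0.025 to the primary endpoint and fixes no alpha for the subgroups, so an openly declared 0.05 for a secondary analysis is debatable but not forbidden. The SD of 16 is labelled a hypothesis. The primary comparison is untouched: with 88 per arm, its power at SD 19 and one-sided 0.025 is about 94%. If the abstract's total does come from the subgroup calculation, the 83% found here exceeds the 80% stated there.

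Most of this stands, and it limits the point. It does not explain why alpha doubles within one paragraph on the same endpoint, or why nearly the same total carries 0.025 and 80% in one place and 0.05 and 90% in another.

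Four stronger readings are tempting but not supported:

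- **An arithmetic error.** The 88 is correct for its inputs. The fault lies in the inputs and in their conflict with the abstract.
- **SD 16 shown to be wrong.** The 29% and the 20 points hold only if 19 is the total SD in this trial's own population, and the 20 points also assume an even age split. The documents establish neither.
- **A false-claim rate near 10%.** Two independent tests at 0.05 give 1 − 0.95² = 9.75%, but only if the true difference sits at the margin in both age groups. The primary test would then fail 97.5% of the time, and the plan does not say that a subgroup claim would stand alone. Subgroup ordering may also be set in an analysis plan that is not shown.
- **Only an 81% chance that both subgroups succeed** (0.9² on the plan's inputs). The plan states power for each subgroup, not for both jointly.

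**Conclusion.** The point holds as a moderate one. The 90% subgroup power depends on a one-sided alpha of 0.05 that is unexplained and is twice that of the main calculation and the primary test. It also does not agree with the abstract. At one-sided 0.025 the power is about 83% if the SD is 16; the change of alpha alone costs about 7 points. The fall to about 69% also requires the SD to stay at 19.

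These figures assume a true difference of zero, a margin of 10 and 88 evaluable patients in each age stratum, which no quota guarantees. That the 0.05 is one-sided is inferred from reproducing the 88; the text does not say so. The conclusion on the primary endpoint and its 76 per arm do not change, so this is not a fault that must be cured before the trial can answer its main question.

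**What to change.** 1. In Sample size and Statistical analysis, state that the age subgroups are tested at one-sided 0.025: the lower limit of the two-sided 95% confidence interval for on-demand minus routine removal, against −10. Call these results supportive, interpreted only after overall non-inferiority is shown.
2. Replace the 90% subgroup power with about 83% (SD 16) and about 69% (SD 19), each stated as conditional on 88 evaluable patients in each age stratum. Say that the SD of 16 is an assumption without supporting data.
3. Reconcile the abstract with Sample size on alpha (0.025 or 0.05), power (80% or 90%), loss (15% or 10%) and total (194 or 193), and say which calculation the total comes from.

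Do not raise the sample size: 90% subgroup power at one-sided 0.025 and SD 16 would take 216 evaluable patients, or 240 randomised with 10% loss (216/0.9), for a supportive analysis. The cost is wording and a less favourable stated subgroup power.

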### Statistical analysis

The primary endpoint will be analysed according to the intention-to-treat and the per-protocol principle, non-inferiority will only be declared if both types of analysis prove non-inferiority. The primary endpoint will be analysed using a one sided test for non-inferiority with an alpha of 0.025. Descriptive methods will be used to assess quality of data, homogeneity of treatment groups and endpoints. Normality of the data will be analysed by visually inspecting the histograms. Secondary outcomes will be analysed using either a t-test or Mann-Whitney U test for continuous data according to the distributing of the data and a Chi Square test for categorical data. Missing data will be handled through multiple imputation with predictive mean matching. All analyses will be performed using the standard statistical software. Separate analyses will be performed on subgroups based on age. A multivariable analysis will be performed to identify predictors of worse functional outcome.

The CEA and CUA will be performed on the intention to treat data, with a time horizon of 12 months and from a societal perspective. The primary economic outcomes are the costs per quality adjusted life year (QALY) and the costs per point functional recovery improvement. Moreover a budget impact analysis (BIA) will be performed with a time horizon of 4 years. The questionnaires estimating the secondary outcome measures ‘resources utilization’ and ‘costs’ will only be used in patients included in the Netherlands due to practical feasibility and to ensure a valid outcome.

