### Randomisation

Randomisation will be stratified by centre and age category (i.e. ≥ 60 years and < 60 years). Randomisation will be blocked within strata. Randomisation sequence is generated by a dedicated computer randomisation software program (CASTOR®, Amsterdam, The Netherlands), ensuring allocation concealment. Randomisation will mostly be performed at the outpatient clinic by coordinating investigator using a dedicated, password protected, SSL–encrypted website.

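### Age category and centre stratify the randomisation, but no overall treatment comparison in the article uses them; naming an adjusted model would gain precision at no cost

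*Protocol article*

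**What the plan says.** - **Allocation.** Protocol article, Randomisation: "Randomisation will be stratified by centre and age category", with the age cut at 60 years and blocking within strata.
- **Primary analysis.** Statistical analysis: "The primary endpoint will be analysed using a one sided test for non-inferiority with an alpha of 0.025". Non-inferiority must hold in both the intention-to-treat and the per-protocol analysis. No test statistic, model or covariate is given.
- **Secondary outcomes.** Same section: "Secondary outcomes will be analysed using either a t-test or Mann-Whitney U test for continuous data", chosen by the distribution of the data, and a chi-square test for categorical outcomes. Normality is judged by looking at histograms. Missing data are to be multiply imputed.
- **Use of age and of regression.** Age appears only in separate subgroup analyses. The one multivariable analysis looks for predictors of poor function; it does not estimate the treatment effect. Centre appears in no analysis.
- **Sizing.** The Sample size section assumes no true difference ("we hypothesized an equal OMAS between the two groups"). One-sided alpha is 0.025, target power is 90%, and the overall SD is taken as 19 from an earlier study. The result is stated as "setting our non-inferiority limit at 10 a total of 76 patients are needed in each study arm". For the age subgroups an SD of 16 is used, because "We hypothesize that the SD will be lower in these subgroups due to increased homogeneity". The total to be randomised is 193, allowing for 10% loss.

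**The concern.** Stratifying by age makes the arms alike in age mix, so differences in outcome between age groups drop out of the true sampling error of the treatment difference. A standard error computed without age still counts that variance. It is therefore too large whenever age predicts the outcome: the interval is too wide and the real one-sided error rate falls below the stated 0.025. The same logic applies to centre.

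This matters here because non-inferiority is decided by whether a confidence limit clears a 10-point margin, and must be shown in two analysis sets. The plan itself assumes that age is strongly related to the outcome, since it lowers the SD from 19 to 16 within age groups.

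A smaller, separate matter concerns secondary outcomes only. A Mann-Whitney test chosen from a histogram takes no covariates and gives no difference in points with a standard error to pool across imputations.

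**Working it through.** **Inputs.** From Sample size: margin 10, true difference 0, one-sided alpha 0.025, SD 19 overall, SD 16 within age group (hypothesised), 76 per arm, 193 randomised, 10% loss. From Interventions: 1:1 allocation.

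**1. The plan's own figure.** n per arm = 2 × SD² × (1.96 + 1.2816)² / margin² = 2 × 361 × 10.508 / 100 = 75.9, so 76. This matches the article and uses the overall SD, with no allowance for covariates.

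**2. Evaluable patients at the planned total.** 193 × 0.90 = 173.7, or 86.85 (about 87) per arm.

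**3. Share of variance due to age, on the plan's SDs.** 1 − (16/19)² = 0.29.

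**4. Standard errors at 86.85 per arm.**
- Unadjusted: 19 × √(2/86.85) = 2.883; half-width 1.96 × 2.883 = 5.65.
- Adjusted for age: 16 × √(2/86.85) = 2.428; half-width 1.96 × 2.428 = 4.76.

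**5. Power.** With age balanced between arms, the true standard error of the difference is 2.428 under either analysis. Write Φ for the standard normal distribution function.
- Unadjusted: Φ((10 − 5.65)/2.428) = Φ(1.79) = 96.3%.
- Adjusted: Φ(10/2.428 − 1.96) = Φ(2.16) = 98.5%.

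**6. Actual one-sided error of the unadjusted test at the margin.** P(Z > 1.96 × 19/16) = P(Z > 2.33) = 0.010, against a nominal 0.025.

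**7. Range.** The SD of 16 is a hypothesis, so the share of variance explained by age is varied. The 10% row is an assumption made here, with within-age SD 19 × √0.9 = 18.02.

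| Variance explained by age | Half-width, unadjusted / adjusted | Power, unadjusted / adjusted | Error rate, unadjusted |
|---|---|---|---|
| 29% (plan's SDs) | 5.65 / 4.76 | 96.3% / 98.5% | 0.010 |
| 10% | 5.65 / 5.36 | 94.4% / 95.5% | 0.019 |
| 0% | 5.65 / 5.65 | 93.4% / 93.4% | 0.025 |

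**8. The same contrast at 76 per arm**, the number sized for the primary comparison: half-width 6.04 against 5.09. A simulation of 20,000 runs, with age balanced between arms and a 50:50 age split, gave power 93.2% against 96.8% and error rate 0.010 against 0.024.

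**9. How plausible is 16?** With a 50:50 age split, an SD of 19 overall and 16 within groups implies a gap in mean OMAS between age groups of 2 × √(361 − 256) = 20.5 points, twice the margin. At a 30:70 split it is √(105/0.21) = 22.4. The 29% row is therefore best read as the upper end of the range.

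No such calculation is possible for centre, because the article gives no between-centre variance.

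**The case against.** The strongest reply is that the article is silent on the primary model and does not prescribe an unadjusted one. It is a condensed account, covariates are commonly settled in the statistical analysis plan, and sizing on the total SD is compatible with a later adjusted analysis. That stands. A reader might infer that the primary analysis is fixed as unadjusted and ignores both factors, but the quoted sentence does not say so. What remains is that no overall comparison the article describes uses the strata, and that the secondary tests it does name cannot.

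A reader might also infer that the trial is underpowered or its test invalid. It is neither. The number per arm was computed on SD 19, so 90% power is met without adjustment, and a conservative test cannot raise the chance of a false claim of non-inferiority above 0.025.

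The size of the gain is also open to challenge. The SD of 16 has no source and speaks to age only. At the planned 193, power is already above its target and the gain is 1 to 2 percentage points. All of this is accepted and sets the size of the point. It does not remove the case for adjusting, since the direction does not depend on the SD of 16: if age explains any variance the adjusted interval is narrower, and if it explains none nothing material is lost.

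Finally, the Mann-Whitney point has nothing to do with the primary confidence limit. That is right; it is kept here for secondary outcomes alone.

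**Conclusion.** The point holds as one of forgone precision. The factors that stratify the randomisation are not carried into any overall treatment comparison the article describes. If the primary test is run unadjusted, its interval will be wider than necessary and its error rate below 0.025 to the extent that age predicts OMAS. At about 87 per arm the interval could be up to 0.9 points narrower each side (5.65 − 4.76 = 0.89) with about 2 percentage points more power. At 10% of variance explained these become 0.3 points and about 1 percentage point, and at none, zero.

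These figures assume a normal approximation, equal SDs in the arms and close age balance between arms. The plan's 90% power and error ceiling are met either way. Nothing in the article supports a numerical claim about centre.

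**What to change.** State in the Statistical analysis section:

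1. The primary difference in 12-month OMAS and its two-sided 95% confidence interval come from a linear model with arm, age category (under 60, 60 or over) and centre, the last as a random intercept or with small centres pooled.
2. With the difference taken as removal on demand minus routine removal, non-inferiority is declared if the lower confidence limit lies above −10 in both the intention-to-treat and the per-protocol analysis, each pooled over the imputations.
3. Continuous secondary outcomes use the same adjusted model in place of a t-test or Mann-Whitney test picked from histograms, so that each gives an estimate that can be pooled across imputations.

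If an analysis plan not shown here already specifies such a model, a sentence pointing to it is enough. The cost is wording only: both variables are already recorded for randomisation, and margin, alpha and sample size are unchanged. The model should be fixed before outcome data are seen by arm.
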